**Figure 1 Fig1:**
[figure not shown]
**Study scheme.** In total 70 patients will be included in the study, 18–75 years old. Patients will be randomised prior to transplantation. Thirty five of these patients will be included in the Certican®/MSC group and 35 patients in the Certican®/standard dose tacrolimus group. All patients will receive steroids (100 mg at day 1 to 3, 50 mg at day 4, 20 mg at day 5 to 15, 15 mg at day 15 to 21, and 10 mg after day 22) and induction treatment with alemtuzumab at day 0 and 1 (15 mg subcutaneously)*. Certican® dose will be 1.5 mg b.i.d. with trough levels between 3 and 8 ng/ml. Tacrolimus will be started orally 3 h before surgery (initial dose 2x5 mg ). In the first 6 weeks target trough levels are aimed at 10 ng/ml (range 8 to 12 ng/ml) for tacrolimus and thereafter 6–8 ng/ml. In the MSC treated group, BM will be harvested just prior to the renal transplantation and MSCs will be cultured in the GMP laboratory. Patients will receive 2 doses of a target of 1,5x10^6^ autologous BM MSCs per/kg body weight IV (range 1-2x10^6^) 7 days apart, 6 and 7 weeks after transplantation. The dose of tacrolimus will be reduced to 50% at the time of the second MSC infusion and completely withdrawn 1 week later. Patients will receive at that time point 15 mg of prednisolone. In all patients a renal biopsy will be performed at 4 weeks and at 6 months and scored according to the Banff criteria.

### Study procedures

Subjects will be seen in accordance with the assessment schedule listed below (Table 1).

**Table 1 Tab1:** **Assessment schedule**

**Baseline**		**Tx date**	**Protocol renal biopsy**	**First MSC infusion**	**Second MSC infusion**								
**Week**		**D0**	**W4 a 5**	**W6**	**W7**	**W8**	**W9**	**W10**	**W12**	**W14**	**W16**	**W20**	**W24**
BM harvesting		X											
MSC expansion, generating		X											
Informed consent	X												
Medical history	X	X	X	X	X	X	X	X	X	X	X	X	X
Concomitant medication	X	X	X	X	X	X	X	X	X	X	X	X	X
Transplantation information	X	X	X	X	X	X	X	X	X	X	X	X	X
Physical examination	X	X	X	X	X	X	X	X	X	X	X	X	X
Routine lab	X	X	X	X	X	X	X	X	X	X	X	X	X
Viral load CMV and BK		X	X	X		X		X		X		X	X
Urinalysis	X	X	X	X	X	X	X	X	X	X	X	X	X
MSC infusion				X	X								
Renal biopsy		X	X										X
Sera for storage		X	X			X			X				X
Iohexol clearance			X										X
Blood for immune monitoring		X	X	X		X			X				X
DSA		X	X#						X				X
Safety assessment	X	X	X	X	X	X	X	X	X	X	X	X	X
Echo cardiography and pulse wave velocity			X										X

Follow up study visits are planned at baseline, day of transplantation, during the renal biopsy (week 4 a 5), during the first and second MSC infusion at week 6 and 7, week 8, 9, 10, 12, 14, 16, 20, 24 after transplantation.

### Isolation of bone marrow and infusion of MSCs

BM will be aspirated from the posterior iliac crest of all patients under general anesthesia during the renal transplantation. A total volume of 100 a 120 ml will be harvested. The processing of the cells will take place at the GMP Stem Cell Laboratory Facility of the LUMC.

In consented patients, a clinical re-evaluation will be undertaken before the planned infusion of MSCs. A target of 1,5×10^6^ MSCs per/kg body weight (range 1-2×10^6^) will be infused within 30 minutes as indicated. Actual doses of MSCs administered will be documented for each patient. Close monitoring of vital signs (temperature, pulse, respiratory rate, blood pressure, and oxygen saturation) will be measured and documented before MSC infusion, every 15 minutes in the first hour and every 30 minutes in the second hour after infusion.

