Thirty five of the patients will be included in the everolimus/MSC group and 35 patients in the everolimus/standard dose tacrolimus group (Figure 1, study scheme). All patients will receive steroids and induction treatment with alemtuzumab at day 0 and day 1 (15 mg subcutaneously). BM will be harvested just prior to the renal transplantation only from patients randomised to the MSC treatment group. MSCs will be cultured in the GMP laboratory, as previously described [34]. Patients will receive 2 doses of a target of 1,5×10^6^ MSCs per/kg body weight (range 1-2×10^6^) at weeks 6 and 7 after transplantation. The dose of tacrolimus will be reduced to 50% at the time of the second MSC infusion and completely withdrawn 1 week later. At that time point the patient will receive 15 mg prednisolon. The expected period of patient accrual is approximately 24 months. All study procedures will take place at the LUMC.

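### The article states two different populations for the bone marrow harvest: the MSC arm only, and all patients

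*Protocol article*

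**What the plan says.** Three places in the protocol article describe who has marrow harvested.

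- **Methods and design, paragraph after the exclusion criteria:** "BM will be harvested just prior to the renal transplantation only from patients randomised to the MSC treatment group".
- **Figure 1 legend:** "In the MSC treated group, BM will be harvested just prior to the renal transplantation and MSCs will be cultured in the GMP laboratory".
- **Isolation of bone marrow and infusion of MSCs:** this procedure section states "BM will be aspirated from the posterior iliac crest of all patients under general anesthesia during the renal transplantation". The next sentence gives the amount: "A total volume of 100 a 120 ml will be harvested".

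The allocation is equal: "Thirty five of the patients will be included in the everolimus/MSC group and 35 patients in the everolimus/standard dose tacrolimus group". The Figure 1 legend adds "Patients will be randomised prior to transplantation", so the arm is known by the time of any harvest.

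**The concern.** The harvest is invasive, and the article gives two incompatible answers to who undergoes it. The design paragraph limits it to one arm with an explicit restriction. The procedure section removes that restriction, and it is the only place that gives the aspiration site, the anaesthesia and the volume. A person carrying out the procedure would naturally look there.

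The issue is what control patients are exposed to. Under one statement they have no marrow aspiration. Under the other they have one, without any MSC infusion to follow. Control patients, and anyone explaining the trial to them, need a single answer.

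**Working it through.** No statistical formula applies. The check sets the statements side by side and counts patients.

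**Inputs**

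| Place in the article | Who is harvested | When |
|---|---|---|
| Design paragraph after the exclusion criteria | MSC arm only | Just before transplantation |
| Figure 1 legend | MSC arm | Just before transplantation |
| Isolation of bone marrow and infusion of MSCs | All patients | During transplantation, under general anaesthesia |

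The allocation is 35 MSC and 35 control, 70 in total. The volume is 100 to 120 ml per harvested patient.

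**Step 1: can the population statements be reconciled as written?** Not literally. A harvest confined to one arm excludes the other arm, and a harvest from every patient includes it. They agree only if the procedure section is read as covering every patient in the MSC arm, a qualifier it does not contain.

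**Step 2: how does the article use the phrase elsewhere?** It covers both arms in three other places: steroids and alemtuzumab induction (design paragraph), the renal biopsies at 4 weeks and 6 months (Figure 1 legend), and cotrimoxazole prophylaxis (the section on opportunistic infections). The same usage in the procedure section would bring in the controls.

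**Step 3: count.**

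- Design paragraph and Figure 1 legend: 35 harvested.
- Procedure section, read literally: 35 + 35 = 70 harvested.
- Difference: 70 − 35 = 35 control patients, and 35 / 70 = 50% of the trial.

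**Step 4: is the timing also a contradiction?** Only weakly. Just before and during transplantation both fall on the day of transplantation (D0) and could describe one session under the same anaesthetic. The wording differs, but the two are not shown to be incompatible.

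**Step 5: does any planned calculation depend on the answer?** No. The sample size section uses a mean fibrosis of 18% against 14%, a standard deviation of 5%, 25 evaluable patients per group and 70% with valid measurements. None of these involves the harvest.

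**The case against.** The best defence is context. The procedure section concerns only the MSC pathway: aspiration, cell processing, infusion and observation afterwards. Its infusion sentences name no arm either, and nobody would take them to mean that controls are infused. All patients may therefore be shorthand for all patients in that pathway. The two places that name an arm agree with each other, and one of them is explicit. This makes a drafting slip plausible and keeps the severity low. It does not remove the conflict, because the qualifier is absent and the article's usage elsewhere points the other way.

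Several stronger readings are tempting, but the article does not support them.

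- **That Table 1 adds a further conflict.** Its row "BM harvesting" names no arm, but neither does its row for MSC infusion. It is one schedule for both arms and contradicts neither statement.
- **That the timing is a second contradiction of equal weight.** Both descriptions fit D0 and a single session.
- **That the answer determines when patients are randomised, and so the exclusions that arise after randomisation.** The article places randomisation before transplantation and gives no reason for it. Nothing links that choice to the harvest, and it stands under either wording.
- **That by-arm reporting of harvest-related adverse events is inconsistent.** The article makes no statement on such reporting, so there is nothing to contradict. That detail is commonly left to the full protocol or analysis plan.

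**Conclusion.** The point holds as an internal inconsistency of minor severity. The design paragraph, supported by the Figure 1 legend, confines the harvest to the MSC arm. The procedure section extends it to every patient. The size is 35 of 70 patients, each with an aspiration of 100 to 120 ml. That figure is a count of the patients whose exposure is stated two ways. It is not an estimate of how many controls would in fact be aspirated. It assumes the planned equal allocation and a literal reading of the procedure section.

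The fibrosis comparison, its power and the timing of randomisation are untouched. The documents do not establish which statement reflects the intended procedure, and this review does not choose between them.

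**What to change.** Reconcile the design paragraph after the exclusion criteria, the Figure 1 legend and the section on isolation of bone marrow and infusion of MSCs, so that all three state the same harvested population. In the same edit, use one wording for when on D0 the harvest takes place. The sponsor should take both from the procedure actually intended and check that the full protocol says the same.

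The cost is a correction of a few sentences. The sample size, the analysis and Table 1 need no change on this account.

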### Data collection

Patients enrolled in this study will undergo standard pre-transplant work-up, which consists of baseline clinical data (demographics, medical history, current medication, previous blood transfusions, percentage of panel reactive antibodies, infection status (see below), physical examination, laboratory examinations, urinalysis, electrocardiogram, chest X-ray, infection screening). For women, the menopausal status will be recorded. The pregnancy test will be done prior to transplantation (according to our standard transplantation criteria). Results must be available and negative prior to administration.

Intraoperative data (warm and cold ischemia time, blood loss) and background information of the donor (age, gender, race, height, weight, type of allograft (living related or unrelated), infection status, serum creatinine) and HLA (mis)match will also be documented. All immunosuppressive and other drugs used and dosages administered will be recorded during the study.

### (Opportunistic) infections

HBsAg, Hepatitis C and HIV evaluated for screening will be performed standard before transplantation. Earlier tests, within 6 months prior to baseline are acceptable. CMV (PCR-positive), EBV (PCR-positive), BK-viruria in urine samples and BK-viremia in blood samples (RT-PCR) will be measured at baseline, week 4, 6, 7, 8, 10, 14, 20 and 24. Other infections (including urinary tract infections, pulmonary infections, herpes simplex) will be recorded as well. Patients are treated routinely with valganciclovir profylaxis per os for 6 months except for a CMV negative donor recipient status. In addition, all patients receive 6 months of cotrimoxazole prophylaxis against pneumocystis jirovecii pneumonia.

### Renal function

Glomerular filtration rate (GFR calculation) will be used to measure the renal function. The following abbreviated MDRD formula will be used for GFR estimation eGFR [mL/min/1.73 m2] = 186.3x SCr-1.154 × Age-0.203 × (0.742 if female) × (1.21 if black). In addition we will measure renal function with iohexol clearance at week 4 and 24. The iohexol clearance will be performed at the day of the renal biopsies.

### Fibrosis scoring by renal biopsy

A standard renal protocol biopsy is performed prior to the transplantation and at 6 months after transplantation. At 4 weeks after transplantation a study biopsy is taken to assess the renal histology before MSC infusion. Biopsies are scored according to the Banff criteria and processed for immunohistochemistry (HE staining; staining for CD3, CD4, CD68, FOXp3, C4d and CD20). In addition, the amount of cortical collagen (SR-positive area) will be measured and finally expressed as the percentage of the total analyzed cortical surface. Moreover, changes in mRNA expression of pro- and anti-fibrotic genes (including FGFb and fibronectin) in renal biopsies taken before and after MSC infusion through real-time quantitative PCR will be performed.

### Cardiovascular follow-up

Left ventricular internal dimension and wall thickness will be measured at end-diastole and at end-systole according to recommendations of American Society of Echocardiography. End diastolic left ventricular septal and posterior wall thicknesses and internal dimensions will be used to calculate left ventricular mass. Echocardiography will be performed at week 4 and week 24.

### Immune modulating capacities before and after MSC infusions

DSAs will be measured at baseline (before transplantation), time of renal biopsy, 12 weeks and 6 months after transplantation and every time a for-cause allograft biopsy is performed. For immunological monitoring, we will collect sera and PBMCs at different times post transplantation as described. Phenotypical analyses of the different leucocyte subpopulations will be performed on basis of the immune panels developed and validated for the One Study [36].

In addition mixed lymphocyte reaction assays of recipient’s PBMCs will be performed sequentially with the use of frozen cells obtained before transplantation to compare responses to the donor cells before and after transplantation [37]. Supernatants of these MLR cultures will be collected for analyses of cytokine profiles. Direct cross-matches of recipient sera and donor lymphocytes will be done by complement dependent cytotoxicity (CDC) and flow-cytometric assays. PBMCs will be stimulated using CD3/CD28 and analyzed for TH1 (i.e. interleukin-2 and interferon-γ), TH2 (IL-10 and IL-4) and inflammatory cytokines (i.e. tumor necrosis factor-α, TGF-β, IL-1 and IL-6).

### Data safety monitoring committee

The DSMB will monitor the safety of subjects. The DSMB consists of two independent physicians and one biostatistician. The DSMB will meet at least after inclusion of 20 and 50 subjects. They will judge on the rate of rejections and serious adverse events (SAEs) in the study. We regard a 30% rejection rate and over to be unacceptable; this will lead to study termination. The DSMB will review all serious adverse events unblinded and determine, based on a careful consideration of the events, whether the SAE is most likely related to MSCs. This review will take all aspects into account, including onset of the SAE relative to MSC infusions, other potential causes for the SAE such as concomitant medication and underlying conditions, and other previous adverse events observed over the course of the study. Only SAE that were assessed by the DSMB as most likely related to MSC will be taken into account for the decision to proceed with the study. The DSMB has the right to terminate the study.

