### Risk-benefit assessment

The high prevalence of nephrotoxicity suggests that CNI are unsuitable as long-term immunosuppressive agents for kidney transplantation and MSCs might offer an alternative treatment modality with the aim to inhibit fibrosis and to prolong allograft survival. In previous studies in transplant recipients, MSC therapy was shown to be feasible and no major serious side effects have been reported so far. One of the risks of CNI withdrawal is an increased risk of acute allograft rejection. Therefore renal function and trough levels of the immune suppressive drugs will be monitored frequently. In addition, the type of induction therapy (alemtuzumab) and the timing of CNI withdrawal (>6 weeks) are chosen to minimize risks for allograft rejection. We think that early clinical results, which suggest beneficial effect from MSC administration for patients after renal transplantation and the expected limited possibility on adverse side effects justify participation in this study.

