
As secondary endpoints safety measures will be included. An important safety issue includes direct toxicity related to the infusions. Although, to date, no toxicity has been observed during intravenous MSC infusion [11], a possible side-effect of MSC transfusion could be a transfusion reaction (e.g. allergic reaction, fever and hypotension). Another possible side effect could be an increased risk of infection; therefore all donors are thoroughly screened before BM aspiration. In addition, one cannot rule out that a renal transplant recipient receiving MSCs might have a decrease of renal function. In addition, the change in immune suppressive regimen might increase the incidence of acute rejection.

Other potential risks which should be considered when using MSCs for clinical applications include risk for malignancies and opportunistic infections. So far, in clinical trials using MSCs no malignancies have been reported. However most trials have a short follow up and we are still awaiting reports on long-term effects [20,62,63]. Moreover, in many trials patients with a poor prognosis are included where MSC-related side effects might be obscured. In addition, due to the concomitant use of immunosuppressive medications, patients who received a renal transplant are already at enhanced risk of malignancies.

The risk of over immunosuppression, which may lead to opportunistic infections, has been studied in a few reports and will be closely monitored in our trial as well. In a study by Tan et al. on patients undergoing renal transplantation [32], the use of autologous MSCs instead of anti-IL-2 receptor antibody induction therapy resulted in decreased opportunistic infections (including CMV infections). However, CMV donor recipient status was negative in 151 of 154 patients, which might have caused the low incidence of CMV infections in their population. In our previous trial, 3 out of 6 renal recipients developed opportunistic infections [34] and also MSC co-infusion after haematopoietic stem cell transplantation (HSCT) caused a higher 1-year incidence of (particularly fungal) infections [64]. It is clear that frequent and accurate monitoring of infectious complications and also monitoring of the level of immune suppression remains essential.

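### Apart from rejection, only SAEs that the DSMB attributes to MSC count toward the decision to proceed, although the randomised strategy is MSC plus tacrolimus withdrawal

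*Protocol article*

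**What the plan says.** The section on the data safety monitoring committee first gives the board a general remit: "They will judge on the rate of rejections and serious adverse events (SAEs) in the study". It then sets a limit for rejection: "We regard a 30% rejection rate and over to be unacceptable; this will lead to study termination". That limit carries no condition about cause.

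It next describes the review of individual events. The board sees every SAE unblinded and decides whether MSC is its most likely cause. It considers timing relative to the infusions, earlier adverse events in the study, and "other potential causes for the SAE such as concomitant medication and underlying conditions". The rule follows: "Only SAE that were assessed by the DSMB as most likely related to MSC will be taken into account for the decision to proceed". The section ends: "The DSMB has the right to terminate the study".

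Under Study design and in the Figure 1 legend, the experimental arm receives two MSC infusions, and tacrolimus is halved at the second and stopped a week later. The control arm stays on standard tacrolimus. The Risk-benefit assessment states: "One of the risks of CNI withdrawal is an increased risk of acute allograft rejection". The Discussion adds that "the change in immune suppressive regimen might increase the incidence of acute rejection", and also discusses infection, malignancy and reduced renal function as possible harms.

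**The concern.** The rule filters safety evidence on one component of a two-component intervention. A patient randomised to the experimental arm is exposed to the cells and to the loss of tacrolimus. An SAE caused by the second component is a consequence of randomisation, but the wording leaves it out of the decision to proceed.

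The rule also sets aside the strongest evidence a randomised trial can offer its board. A control patient receives no MSC, so a control-arm SAE can never qualify, and the criterion has no place for a comparison of arms. An excess in the experimental arm enters only if its events are attributed to MSC one at a time, at the most-likely standard.

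That attribution is hard here. All patients receive alemtuzumab, everolimus and steroids, and the board is told to weigh concomitant medication as a competing cause. The article's account of the phase 1 study shows the difficulty: opportunistic viral infections occurred in 3 of 6 patients, and the authors went no further than saying that MSC might have played a part. The same signal in this trial could fail the standard.

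What is at stake is whether a real excess of serious harm, in full view of the board, may be used when it decides whether to continue.

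**Working it through.** The point concerns a decision rule, and the article gives no SAE rate, so there is no plan figure to reproduce. The check is to apply the section's two explicit criteria to each type of event.

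| Event in the experimental arm | 30% rejection rule | SAE criterion for proceeding |
|---|---|---|
| Rejection, any cause | counts | counts only if attributed to MSC and serious |
| Other SAE, attributed to MSC | not covered | counts |
| Other SAE, attributed to withdrawal, other drugs or underlying disease | not covered | does not count |
| Excess of other SAEs over control, not attributed event by event | not covered | does not count |

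The last two rows are the gap. They contradict the remit sentence, which speaks of the rate of SAEs without a filter.

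**Rejection below the limit.** The arm or denominator for the 30% is not stated. With 25 patients per arm:
- Read on the MSC arm, 7/25 = 28% against 1/25 = 4% in control does not reach the limit.
- Read on both arms pooled, 10/25 and 2/25 give 12/50 = 24%, which does not reach it either.

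In both cases the serious rejections attributed to withdrawal would also be outside the SAE criterion.

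**How much of an excess could be lost.** This illustration uses assumed rates that are not in the documents: 30% of control and 60% of experimental patients with an SAE. The minimum looks are at 20 and 50 subjects, about 10 and 25 per arm under 1:1 allocation. The expected excess is n × (0.60 − 0.30), which is 3.0 patients at n = 10 and 7.5 at n = 25. If a share q of the excess is attributed to MSC, the rule counts q times that number:

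| q | 10 per arm | 25 per arm |
|---|---|---|
| 0% | 0 | 0 |
| 25% | 0.75 | 1.9 |
| 50% | 1.5 | 3.75 |
| 100% | 3.0 | 7.5 |

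The documents do not fix q, so the whole range is open. The table shows only that the excess enters through attribution and by no other route.

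**Precision of a between-arm comparison at the looks.** Under the same assumed rates, the approximate 95% half-width is 1.96 × √[(0.30 × 0.70 + 0.60 × 0.40)/n] = 1.96 × √(0.45/n).
- n = 10: 1.96 × 0.212 = 0.42, so 30 points with an interval of about −12 to 72.
- n = 25: 1.96 × 0.134 = 0.26, so about 4 to 56.

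Even a large excess is estimated roughly at these looks.

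**The case against.** The strongest defence is that the section should be read as a whole. Rejection, the only harm that the article ties to withdrawal or to the regimen change, is governed by a rule with no attribution filter. The board reviews all SAEs unblinded. Its right to terminate comes after the filter sentence and carries no condition. Attribution is not purely event by event either, since earlier adverse events in the study are considered, so an accumulating pattern can inform it. A DSMB charter, not shown here, may add tables by arm. Comparisons at 10 and 25 patients per arm are imprecise, as the working shows.

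Much of this stands, and it rules out stronger readings that a reader might infer:
- That all serious harm from withdrawal is discarded. This is not true of rejection, which counts toward the 30% limit whatever its cause.
- That the board could not act on other harm. It sees every SAE and may stop the trial.
- That almost every serious infection or death would drop out. The test is the most likely cause, not the absence of any other cause, and the article itself treats infection as a possible MSC effect. Harm from the combined regimen counts if the board attributes it to MSC.

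The defence does not remove the defect. The 30% rule covers rejection alone. The right to terminate does not say what evidence supports it, while the sentence before it says which SAEs may inform the decision to proceed; at best the two conflict. A charter that weighed all SAEs would contradict the word that opens the filter sentence. Imprecision is a reason to read the comparison with care, not to exclude it.

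**Conclusion.** The point holds in limited form. This is a stated rule that gives the wrong result, not a detail left to another document. Followed as written, it bars from the decision to proceed every non-rejection SAE not attributed to MSC, every excess of SAEs over control not attributed event by event, and serious rejections attributed to withdrawal while the 30% limit is not reached. It conflicts with the remit to judge SAE rates and with the unconditional right to terminate.

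No magnitude can be derived from the documents. The SAE rates and attribution shares above are assumptions, and the counted part of an excess can lie anywhere from none to all. The conclusion needs only the wording of the section and the fact that tacrolimus withdrawal is part of the randomised strategy.

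**What to change.** Delete the filter sentence. State instead that the decision to proceed considers all SAEs, deaths and graft losses, tabulated by randomised arm with denominators, whatever their attribution. Show attribution (to MSC, to tacrolimus withdrawal, or to both) beside the counts as supporting information. Reconcile this text with the rejection sentence, including the arm or denominator to which the 30% refers, and with the right to terminate, so that the section states one consistent basis for decisions. A between-arm difference with a confidence interval is optional at these looks.

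The cost is a few sentences in the protocol and the DSMB charter. The trial is open-label and the board already receives all SAEs unblinded, so no new data are needed. The change concerns which evidence the board may use; it sets no threshold and no treatment rule. The downside is that background SAEs add noise, and comparisons at about 10 and 25 patients per arm will be imprecise.
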